### Process Evaluation

We will examine process evaluation measures as a proxy for app use. These will be reported in three categories: (1) app use based on app analytics data provided by Google Analytics, (2) drinking analytics based on server interactions, and (3) notifications sent by the server. Where appropriate, these will be summarized as either median with IQR or mean with SD.

### Access to Study Data

All study data will be made available in an anonymized format alongside any source code via the Open Science Framework. There are no contractual agreements that limit access to, or the sharing of, data.

### Data Management

Data collected in this study will be stored on Google Firebase servers located in the United Kingdom, with audited and copied in real time to Google BigQuery data storage to ensure data integrity. Access to these systems is protected using Google authentication and a zero-trust modal. Upon completion of the study, data will be extracted from the Google Firebase servers and Google BigQuery and compared for assurance and data quality.

During active data collection, the research team (DL and GW) will monitor incoming data to ensure that each platform functions correctly. The research team will not contact participants outside of automatic messaging unless they reach out to the research team with queries (managed by GW; eg, with technical issues concerning how to perform a task or if risk alerts are triggered).

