## Methods

### Ethical Considerations

This study was approved by the ethics committee of King’s College London (LRS/DP-22/23-36879). The study has been registered prospectively on ClinicalTrials.gov (NCT05970484). After completing outcome questionnaires (day 84) at the primary end point (day 84), participants will receive a US $25 (£20 GBP) Love2Shop voucher. There will be no cash alternative offered to participants. We will seek informed consent from all participants via the eligibility and consent survey before the collection of any personal data. For participants in the intervention arm, we will additionally ask for specific on-device permissions to enable the full functionality of the DrinksRation app (eg, to receive push notifications or share health tracking data; refer to the example screenshots presented in Figure 1). Participants can change these optional permissions at any time via the settings page of the app.

Participants will be informed via the participant information sheet that they can withdraw from the study or withdraw from data collection at any time. For participants who withdraw from the study, we will (1) attempt to collect follow-up information if they agree to continued data collection and (2) retain their existing data if they agree to their use. Alternatively, withdrawn participants can delete their study data by contacting the research team. Participants in the control arm will need to withdraw by contacting the research team, whereas those in the intervention arm can withdraw via the app.

If participants in the intervention arm withdraw, they will be asked to delete the intervention app and denied further access. All data, including those from withdrawn participants, except for those who make a request for their data to be deleted, will be included in the final analysis.

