#### Control Arm

The control arm will receive access to the BeAlcoholSmart PWA. A PWA is a website that looks and behaves like a smartphone app. The PWA can take advantage of smartphone features such as push notifications and haptics without requiring the participant to download it via an app store. The BeAlcoholSmart PWA will be accessible to participants in the control arm via a unique link. The app will contain a 7-day alcohol unit calculator and generic public health guidance on safe drinking [20]. Participants will also receive reminders via email prompting them to consult the guidance provided as part of the BeAlcoholSmart PWA. Control participants will be invited to complete all questionnaires via Qualtrics (Qualtrics International Inc), with an email reminder being sent when they are due.

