### Sample Size Calculation

A power calculation was performed based on previously reported data from the DrinksRation RCT [12]. With 148 participants (n=74, 50% per arm), we will have at least 80% power to detect a difference in alcohol consumption of 3 units (approximately 30 g of alcohol/wk) between the intervention and control arms at the 84-day follow-up assessment. This calculation assumes an SD of 5.6 units, an attrition rate of 40% by day 84, a correlation between successive follow-up assessments of 0.7, and an α of 5%.

We have chosen a minimum difference of 3 units based on treatment effects observed in similar studies [26-28] and in reductions observed in the DrinksRation feasibility trial [11] and the confirmatory RCT among help-seeking veterans [12], which found reductions at 28 days of 22 units between the arms. We have chosen a smaller minimum difference of 3 units, recognizing that treatment effects for brief interventions reduce over time and that the target population for this study is not a help-seeking population.

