### Randomization and Blinding

Randomization will be conducted automatically when a token code is generated alongside a unique proxy identifier (managed by researcher GW). At this point, participants are automatically randomized to receive the control or intervention arm and are blinded. The randomization procedure is carried out automatically via a randomization algorithm with no human involvement except to provide a proxy identifier. As allocations are generated dynamically, it is not possible to view future allocations. Researchers DL and GW will be unblinded to treatment allocation to enable the management of the BeAlcoholSmart and DrinksRation platforms as well as participant recruitment and retention, whereas researcher EC will be unblinded to treatment allocation to prepare statistical reports. Researchers DL and EC will not be involved in any participant engagement or recruitment. All other members of the study team will be blinded to treatment allocation.

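### A control participant who misses the day-84 drinking report gets no stated second attempt, and the contact rules conflict with follow-up and reminders promised elsewhere

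*Protocol article*

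**What the plan says.** All references are to the protocol article.

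- **Data Management.** During active data collection, "The research team will not contact participants outside of automatic messaging unless they reach out to the research team with queries". The bracket that follows gives technical problems and triggered risk alerts as examples.
- **Control Arm.** Controls complete questionnaires through Qualtrics, "with an email reminder being sent when they are due".
- **Messaging.** Controls are emailed on joining and when outcome measures fall due, and any further notification is excluded. Intervention women receive push notifications, some of them on particular days to flag inactivity or an outstanding questionnaire.
- **Intervention Arm.** All questionnaires are completed in the app, with push prompts every few hours on the due day.
- **Ethical Considerations.** Push permission is optional and can be changed at any time. For women who withdraw, the team will "attempt to collect follow-up information if they agree to continued data collection". Withdrawn intervention women are asked to delete the app and lose access to it. A £20 voucher rewards day-84 completion.
- **Study Design, Overview.** Controls are to have weekly reminders to use the unit calculator.
- **Randomization and Blinding.** Two researchers are unblinded to manage the platforms "as well as participant recruitment and retention".
- **Sample Size Calculation.** "With 148 participants (n=74, 50% per arm), we will have at least 80% power" for a 3-unit difference at day 84, with SD 5.6, correlation 0.7, α 5% and "an attrition rate of 40% by day 84".
- **Statistical Analysis.** A mixed model uses days 28, 56 and 84 and keeps anyone with at least one follow-up. Effects are estimated at each follow-up separately.

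**The concern.** The primary endpoint is one self-completed form at day 84, and the plan expects about 59 of 148 women (0.40 × 148 = 59.2) to be lost by then. The Discussion names recruiting and retaining enough women as the first challenge. Even so, the contact rules as written leave some women with no stated route to a late response. They also make commitments that cannot all be met.

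The stake is mainly bias. The mixed model handles missing day-84 values by assuming they are missing at random given the data in the model, and the trial's own data cannot test this. Women with no follow-up at all leave the analysis, although it is labelled intention-to-treat. Each late form recovered reduces both problems.

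**Working it through.** **1. Routes to a late day-84 form**

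| Participant | Automated prompt stated | Staff contact |
|---|---|---|
| Control, misses due date | Due-date email only; further notifications excluded | Barred unless she makes contact |
| Intervention, push allowed | Repeated push on due day; further push on particular days | Barred unless she makes contact |
| Intervention, push declined or app removed | None stated | Barred unless she makes contact |
| Intervention, withdrawn in the app, agrees to more data collection | None stated; app access removed | Barred unless she makes contact, yet an attempt is promised |

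Rows 1, 3 and 4 have no stated second attempt. Row 2 does have further prompts, although the article does not say they follow a missed day 84.

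**2. Statements that conflict**

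- *Withdrawal follow-up against the no-contact rule.* Controls withdraw by contacting the team, which fits the rule's exception. Intervention women can withdraw in the app without any contact. They then lose the only questionnaire route described for their arm, so the promised attempt has no stated means.
- *Weekly calculator reminders against the closed list of control emails.* Outcome measures fall due for controls only at days 0, 28, 56 and 84 (Table 1), so due-date emails cannot supply weekly reminders.
- *Retention role against the no-contact rule.* Retention could be run through the automated platforms, so this is a tension and not a flat contradiction.

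**3. Sample size: reproducing 148**

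Inputs from Sample Size Calculation: difference 3, SD 5.6, r = 0.7, 40% attrition, α 5% (two-sided assumed), power 80%. Three follow-ups come from Statistical Analysis.

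- Variance factor for the mean of three follow-ups: (1 + 2 × 0.7)/3 = 0.80
- SD of that mean: 5.6 × √0.80 = 5.009
- n per arm = 2 × (1.960 + 0.842)² × 5.009² / 3² = 43.8, rounded up to 44
- Inflated for loss: 44/0.60 = 73.3, rounded up to 74 per arm, or 148 in total

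This matches the plan exactly, so the 40% loss is already built into the sample size.

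**4. What lower loss would add**

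With 74 randomised per arm, n = 74 × (1 − loss) and power = Φ(3 / (5.009 × √(2/n)) − 1.960). The 30% and 20% rates are assumptions; the article gives no loss rate under reminders.

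| Loss | n per arm | Power |
|---|---|---|
| 40% (plan) | 44.4 | 80.6% |
| 30% | 51.8 | 86.2% |
| 20% | 59.2 | 90.3% |

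Reaching 30% loss means recovering about 15 women (0.10 × 148 = 14.8). Reaching 20% means recovering about 30 (0.20 × 148 = 29.6).

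**The case against.** Much can be said for the plan, and several stronger readings fail.

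- *A reader might infer that a missed day-84 form is never chased in either arm.* The messaging section gives the intervention arm inactivity and questionnaire reminders on particular days. The gap is firm only for controls and for intervention women without push or without the app.
- *A reader might infer that a woman who misses the due day is lost.* Nothing says the form closes that day. Late-response windows are commonly left to a full protocol, so a missing window is not itself an error. What remains is that the article closes the control list and bars staff contact in positive terms.
- *A reader might infer that the rule causes the 40% loss.* That figure is a planning assumption, and nothing ties it to the contact rule. The voucher and asking the TLFB first are real retention measures.
- *A reader might infer a power shortfall.* An unadjusted day-84 comparison with 44.4 per arm has 71.4% power and would need about 25% loss to reach 80%. But that leaves out the stated correlation, the earlier follow-ups and the baseline covariate. If the baseline correlation were also 0.7 (an assumption), the SD would be 5.6 × √(1 − 0.49) = 4.0 and power 94.2%. Any doubt here concerns the sample-size method, not the contact rule.
- *A reader might see conflicts with safety contact and interview invitations.* Both are weak. The Data Management bracket names risk alerts, and Adverse Events assigns contact to the study clinician. Interviews follow day 84 (Table 1 footnote), at or beyond the end of active data collection.

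**Conclusion.** The point holds in a limited form. As written, the plan gives no stated second attempt at the day-84 TLFB to controls, or to intervention women who decline push or remove the app. The contact rules contradict the promised follow-up of women who withdraw in the app and the weekly reminders for controls, and they fit poorly with the staff retention role.

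Correcting this would mean less missing primary-outcome data, less weight on the missing-at-random assumption, and fewer women excluded for having no follow-up. The added precision is secondary: 80.6% power would become 86.2% or 90.3% if loss fell to 30% or 20%. Those figures rest on assumed loss rates, a two-sided 5% test and the mean-of-three method, which reproduces 148 but is inferred. The article does not show how many late forms reminders would recover. This is worth changing before recruitment, but it does not invalidate the design.

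**What to change.** 1. Reconcile Ethical Considerations, Study Design (Overview), Randomization and Blinding, Messaging and Data Management, so that they give one account of who may be contacted, by what route and for what purpose.
2. Exempt outcome collection from the no-contact rule, including follow-up of withdrawn women who agree to it.
3. Send automated emails after each missed due date, identical in timing and wording in both arms so that the change does not itself create a difference in prompting. Link each to a TLFB-only form that opens outside the app.
4. State an acceptance window and record the completion date.

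The reminders can be automated and need no staff chasing. The downside is a few more messages and some day-84 reports that describe a later week. A form completed k days late asks about days 77 + k to 83 + k, so at 7 or more days late the recall week starts on or after day 84 (77 + 7 = 84). The acceptance window should be chosen with that in mind, and the recorded date lets the analysis examine late forms separately.

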## Results

RCT recruitment will begin in January 2024 and last for 5 months. We aim to complete all data collection, including interviews, by May 2024. The results of this study will be communicated via publication, lay articles disseminated via stakeholders and collaborators, and a participant newsletter.

The study will be reported following the TIDieR (Template for Intervention Description and Replication) [38] checklist as well as the CONSORT (Consolidated Standards of Reporting Trials) [39] and CONSORT-EHEALTH (Consolidated Standards of Reporting Trials of Electronic and Mobile Health Applications and Online Telehealth) [40] checklists.

## Discussion

### Summary

This project aims to tailor the DrinksRation app to reflect the specific needs of female veterans and evaluate these changes using a confirmatory RCT. We hypothesize that a refined version of DrinksRation will be efficacious at reducing self-reported weekly alcohol consumption among female veterans who drink at a hazardous or harmful level. Alcohol misuse is a persistent problem in the UKAF, with estimates forecasting that >50% of those who have left the UKAF meet the criteria for hazardous alcohol use. This is almost double that of the general population [41] and higher in female veterans. Innovative digital interventions can be used to great effect to meet this growing demand for support and treatment for alcohol misuse [42,43].

Currently, there are no smartphone-based alcohol interventions targeting female veterans of the UKAF to reduce alcohol misuse. Therefore, we propose to refine DrinksRation—a theory-driven and user-centered smartphone app—to address this gap for female veterans. Although DrinksRation has been tested in a largely male population, there has been little focus on female veterans. This study protocol describes the design of an RCT to determine the efficacy of DrinksRation among a female veteran population.

The Ministry of Defence Research Ethics Committee and the National Institute for Health and Care Research have identified female veterans as an underserved group regarding support and treatment for alcohol misuse. This is often due to medical services targeting male counterparts, failing to target specific female barriers to care, and a general lack of awareness of female motivations for drinking [17,18,44]. Given the limited evidence to date, there is an urgent need for innovation to support female veterans.

A key strength of this study protocol is the collaboration among the charitable sector, stakeholders, academia, and the UKAF, enabling the development and public release of DrinksRation. A further strength includes remote delivery via a smartphone to overcome issues related to availability or geographic limitations for participants. Furthermore, DrinksRation is unique in that it uses personalized push notifications to promote positive changes in behavior among participants [45]. This ensures longer-term engagement and adherence. DrinksRation can also be used on any iOS and Android device released in the last 7 years. However, owing to personalization, the app requires an active data connection to function.

This study will not be without challenges, the first of which concerns our ability to recruit and retain a sufficient number of female veterans to power our analysis. This is due to a known issue: many of those who have alcohol-related problems are reluctant to seek help to ameliorate their problems. We planned our recruitment approach following best practice and our prior experiences in recruitment to mitigate this issue. Furthermore, the app has been designed to promote its active use, with frequent reminders, which is expected to promote adherence to the app. Second, we expect that some participants may encounter technical issues related to the app (eg, unable to log drinks or receive notifications) or the mobile device. To mitigate potential technical or mobile device issues, we have undertaken extensive testing across a range of popular mobile devices, and we will allow participants to provide in-app feedback that will be regularly monitored by the research team. Third, participants may reduce engagement or disengage in the control arm because BeAlcoholSmart is a static service. We will mitigate this by promoting its use to participants and ensuring that all information and data are presented appropriately. Finally, we acknowledge that our sample comprises participants who may be undergoing active treatment. To mitigate this risk, we will measure and describe the number of participants in each arm already receiving treatment for alcohol.

### Open Access Statement

For the purposes of open access, the author has applied a Creative Commons attribution (CC BY) license to any accepted author manuscript version arising from this submission.

### Conclusions

If this study is successful, the DrinksRation platform along with its refined features could be used not only to support women who have served in the UKAF but also for other conditions and disorders.

## Appendix

Multimedia Appendix 1 Behavior change technique assignment to each DrinksRation component.

Multimedia Appendix 2 Eligibility and consent questionnaire.

Multimedia Appendix 3 Questionnaire set.

Multimedia Appendix 4 Drinks menu alcohol unit assignment.

Multimedia Appendix 5 Peer-review report by the Cabinet Office – Office for Veterans Affairs – UK Government.

## Abbreviations

BCT: behavior change technique
CONSORT: Consolidated Standards of Reporting Trials
CONSORT-EHEALTH: Consolidated Standards of Reporting Trials of Electronic and Mobile Health Applications and Online Telehealth
NHS: National Health Service
PAB: patient advisory board
PMG: project management group
PTSD: posttraumatic stress disorder
PWA: progressive web application
RA: research assistant
RCT: randomized controlled trial
SAB: stakeholder advisory board
TIDieR: Template for Intervention Description and Replication
UKAF: United Kingdom Armed Forces
